### Statistical analysis

The analysis will be based on the intention-to-treat principle and will include all outcomes occurring from randomisation to a common study end date. Follow-up will continue until 97 primary outcome events have been accrued in the standard of care arm. Primary endpoint survival times will be depicted using the Kaplan–Meier survival curves and formally assessed using a Cox proportional hazards model which will adjust for study site, age, sex and previous coronary artery disease (the variables on which the randomisation was stratified). The results will be expressed as a hazard ratio with the corresponding 95% confidence intervals and *p*-value.

Secondary outcomes will be analysed using appropriate methods—logistic regression for binary outcomes and linear regression for normally distributed continuous outcomes. Continuous outcomes that are not normally distributed will be analysed using appropriate nonparametric techniques. Subgroup analysis on the primary outcome is planned for participants: (i) sex, (ii) age, (iii) with and without a previous diagnosis of coronary artery disease at randomisation, (iv) with and without preventative therapy (statin and anti-platelet agent) at randomisation, (v) above and below the sex and assay-specific median maximum high sensitivity cardiac troponin concentration at presentation. These will be assessed by examining the effect of the intervention by subgroup interaction in the Cox regression model.

The influence of any missing data on the robustness of the findings will be examined using multiple imputation models under a missing at random assumption. All statistical analyses will be pre-specified in a comprehensive statistical analysis plan, authored by the study statisticians and agreed by the independent study oversight committees.

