### Primary endpoint

The primary endpoint is a composite of myocardial infarction or cardiac death. Myocardial infarction is defined according to the Fourth Universal Definition of Myocardial Infarction [17] whilst cardiac death is defined as death resulting from an acute myocardial infarction, sudden cardiac death, or death due to heart failure [18]. Both myocardial infarction and cause of death will be adjudicated by two independent clinicians blinded to trial intervention with any discrepancies resolved by a third clinician as described previously [19].

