### Secondary endpoints

The secondary endpoints include clinical, patient-centred, process and cost-effectiveness. These are detailed in Table 1.

**Table 1 Tab1:** Secondary endpoints

1. Clinical and patient-centred endpoints	• Myocardial infarction • Cardiac death • Cardiovascular death • Non-cardiovascular death • All-cause death • Unscheduled urgent coronary revascularisation • Hospital reattendance with suspected acute coronary syndrome • Proportion of patients with major bleeding (BARC 3–5) • Symptomatic status as assessed by the short form Seattle Angina Questionnaire (SAQ-7) up to 24 months of randomisation • Quality of life as assessed by the EQ-5D-5L up to 24 months of randomisation • Lifestyle changes including diet, smoking habit, and exercise at 24 months
2. Process endpoints	• Proportion of patients with allergy, anaphylaxis or acute kidney injury following study CTCA scan • Proportion of patients with clinically significant abnormal non-cardiac findings on study CTCA scan • Radiation dose from study CTCA scan • Proportion of patients undergoing non-study CTCA or invasive coronary angiography within 90 days of hospital attendance • Proportion of patients undergoing non-invasive stress test within 90 days of hospital attendance
3. Cost effectiveness endpoints	• Proportion of patients prescribed therapies for coronary artery disease • Proportion of patients undergoing non-invasive stress testing • Proportion of patients undergoing coronary revascularisation • Incremental cost per quality-adjusted life year (QALY) gained

*Abbreviations*: *BARC* Bleeding Academic Research Consortium definition of bleeding [20], *CTCA* computed tomography coronary angiogram

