### Sample size calculation

Based on the event rate in the High-Sensitivity Troponin in the Evaluation of patients with suspected Acute Coronary Syndrome (High-STEACS) trial [19], myocardial infarction or cardiac death will occur in 7.2% of the study population at 24 months. The Scottish COmputed Tomography of the HEART (SCOT-HEART) trial [25] reported a 41% reduction in fatal and non-fatal myocardial infarction in those randomised to CTCA (hazard ratio 0.59 [95% CI: 0.41 to 0.81]), with the treatment effect of the intervention apparent at 36 months. It is anticipated that at a median follow-up of 36 months the event rate in the standard of care arm will be 9%. In the proposed study, for 90% power at an alpha of 0.05, 1081 participants will be required in each arm to detect a 40% relative risk reduction in the primary composite endpoint. To account for drop out of 5%, the aim is to recruit at least 2270 patients to the study. With this sample size, there will be 81% and 67% power to detect a 35% and 30% relative risk reduction if the intervention is less effective. Likewise, the sample size would have 99% power to detect a 50% relative risk reduction if CTCA is as effective in the study population as in those with stable chest pain [26]. With this sample size, it is estimated that 97 primary outcome events will be accrued in the standard care arm of the trial at a median follow-up of 36 months. The data monitoring committee (DMC) will review all primary outcome events intermittently and will inform the trial steering committee (TSC) when this target has been met.

On April 25, 2022, a blinded assessment of the number of events accrued in the first 1925 participants was undertaken and the DMC concluded the trial would not reach the number of primary outcome events required by the planned follow-up date of September 2024. This was a consequence of interruptions to recruitment due to COVID-19 with most participants having less than 12 months follow-up at this point. To minimise the likelihood that follow-up will need to be extended, the DMC and TSC recommended recruitment continue beyond the sample size of 2270 patients. Recruitment of up to an additional 900 participants (total 3170 participants) was completed in May 2023. This should ensure 97 primary outcome events are accrued in the standard care arm by August 2024.

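### Minor point: Kaplan–Meier curves for MI or cardiac death will modestly overstate the probability of the endpoint, because deaths from other causes are competing events; cumulative incidence curves avoid this at almost no cost.

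*Protocol article*

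**What the plan says.** All references are to the protocol article.

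- **Primary endpoint:** "The primary endpoint is a composite of myocardial infarction or cardiac death". The fatal part is narrow: "cardiac death is defined as death resulting from an acute myocardial infarction, sudden cardiac death, or death due to heart failure". Cause of death is adjudicated by clinicians blinded to the trial intervention.
- **Secondary endpoints, Table 1:** other deaths are recorded separately. Cardiovascular death is one item, and the list continues with "Non-cardiovascular death • All-cause death".
- **Statistical analysis, graphical display:** "Primary endpoint survival times will be depicted using the Kaplan–Meier survival curves".
- **Statistical analysis, formal comparison:** the endpoint is "formally assessed using a Cox proportional hazards model which will adjust for study site, age, sex and previous coronary artery disease", and "The results will be expressed as a hazard ratio with the corresponding 95% confidence intervals" and a p-value.
- **Sample size calculation:** the planning figure is that "at a median follow-up of 36 months the event rate in the standard of care arm will be 9"%.

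The article does not mention competing risks and does not say how deaths outside the endpoint enter the curves. It refers all analyses to a statistical analysis plan, which is not shown.

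**The concern.** A participant who dies of cancer, or of a vascular cause outside the definition of cardiac death, before any primary event can never have that event. Kaplan–Meier has no state for this. It censors the participant, which treats the remaining risk as if it were the same as that of people still alive and under follow-up. The result, 1−KM, estimates the probability of the endpoint in a setting where nobody dies of anything else. It exceeds the proportion of patients who will have the endpoint whenever such deaths occur.

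Three features mean that some competing deaths must be expected. Randomisation is stratified at age 70. The eligibility criteria state no upper age limit. The earliest recruits will have been followed for nearly 5 years: recruitment began in September 2019 and the event target is expected to be met by August 2024. The excess grows with follow-up, so it is largest at the right-hand end of the curve.

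At stake is how the main figure is read. Readers take absolute risk from it, and the Discussion itself says that the likely effectiveness of the strategy depends strongly on the cardiac risk of the population tested.

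**Working it through.** **The plan's own figures.** The article plans on 9% versus 5.4% (a 40% relative reduction), 90% power and two-sided alpha 0.05. The usual two-proportion formula without continuity correction gives 1082 per arm, against 1081 stated. The event target follows from 1081 × 0.09 = 97.3, that is 97. These figures reproduce, and nothing below alters them.

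**Inputs for the check**

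- Standard care: 1−KM = 9.0% at 36 months. The article calls this an event rate at a median follow-up of 36 months; reading it as 1−KM at 36 months is my assumption.
- CTCA arm: 1−KM = 0.60 × 9.0% = 5.4%.
- Death from other causes at 3 years, q: not given in the article. Assumed to be 3%, 5% or 8% and equal in both arms, with 1% and 15% as outer values.
- Constant cause-specific hazards (assumed).

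**Formulas.** Let h be the hazard of the primary event and g the hazard of death from other causes.

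- h = −ln(1 − 0.09)/3 = 0.03144 per year
- g = −ln(1 − q)/3 = 0.01015, 0.01710 or 0.02779 per year for q = 3%, 5% or 8%
- 1−KM at time T = 1 − exp(−hT)
- Cumulative incidence at T = [h/(h+g)] × [1 − exp(−(h+g)T)]

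**Example, q = 5%, T = 3.** h/(h+g) = 0.03144/0.04854 = 0.6477. 1 − exp(−0.04854 × 3) = 0.1355. The product is 0.0878, or 8.78%, against 9.0%.

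**Standard care arm**

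| q at 3 years | 1−KM, 36 months | Cumulative incidence | Excess (points) | 1−KM, 5 years | Cumulative incidence | Excess (points) |
|---|---|---|---|---|---|---|
| 3% | 9.0% | 8.87% | 0.13 | 14.5% | 14.2% | 0.35 |
| 5% | 9.0% | 8.78% | 0.22 | 14.5% | 14.0% | 0.59 |
| 8% | 9.0% | 8.64% | 0.36 | 14.5% | 13.6% | 0.94 |

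Excesses are taken before rounding. At the outer values, the 36-month excess is 0.04 points (q = 1%) and 0.68 points (q = 15%).

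**Between arms at 36 months.** A 1−KM of 5.4% in the CTCA arm corresponds to a cumulative incidence of 5.32%, 5.27% or 5.18% for q = 3%, 5% or 8%. The difference between arms falls from 3.60 points to 3.55, 3.51 or 3.46. The risk ratio stays at 0.60, because the relative excess is almost the same in both arms.

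**The case against.** The strongest reply is that the curves serve only as a display. The formal assessment is the Cox model and the stated result is a hazard ratio. A Cox model that censors deaths from other causes is a valid comparison of cause-specific hazards, so nothing that decides the trial is harmed. That stands, and it is why the point is minor.

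A reader might infer more: that the risk difference, a number needed to scan and the cost-effectiveness results will all be inflated. The article does not support this. It names no absolute risk, risk difference or number needed to scan as a result of the curves. The Cost-effectiveness analysis section builds within-trial QALYs from EQ-5D-5L and survival times, costs from resource use, and longer-term values from an adapted existing model; none of this is tied to the primary-endpoint curve. Nor does the article plan Kaplan–Meier curves for the single components of the composite.

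A second reply is that competing risks belong in the statistical analysis plan. The article's silence on them is indeed no fault, and that plan may well add cumulative incidence. But the article does name an estimator, and that estimator does not match the endpoint it defines. This part of the point stands. That deaths from other causes would be censored is inferred, though Kaplan–Meier leaves no other way to estimate this endpoint.

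Third, competing mortality may be low. The share of participants aged 70 or over is not given, and patients may be excluded for limited life expectancy. This is fair, and it favours the lower end of the assumed range.

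**Conclusion.** The point holds as a minor one. The direction is certain: if any participant dies of another cause before a primary event, 1−KM overstates the probability of the endpoint. The size is modest, at 0.13 to 0.36 points on 9.0% at 36 months for assumed mortality from other causes of 3% to 8%. At 5 years the excess is 0.35 to 0.94 points on 14.5%, but median follow-up is expected to be 36 months and only the earliest recruits come near 5 years.

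These sizes rest on constant hazards, on reading the planned 9% as 1−KM, and on a rate of death from other causes that the article does not give. The hazard ratio, its p-value, the target of 97 standard care events and the sample size are not affected.

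**What to change.** In the statistical analysis plan and the report, replace the Kaplan–Meier curves for the primary endpoint with Aalen–Johansen cumulative incidence curves by arm. The competing event is death from any cause outside the definition of cardiac death, occurring before a primary event. Take any absolute risk that is reported from these curves. Keep the adjusted Cox model as the primary analysis, state that deaths from other causes are censored in it, and label the result a cause-specific hazard ratio.

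The cost is a few sentences of wording and a different plotting routine. Cause of death is already adjudicated and other deaths are already recorded, so no new data are needed, and the primary test and the power do not change.

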### Initial hospital attendance, screening visit or telephone contact

During the initial emergency department or equivalent acute medical admissions unit attendance, study visit or telephone contact, the research team will review participants’ clinical history including cardiovascular risk factors, past medical history, standard clinical biochemical and haematological variables, high-sensitivity cardiac troponin concentrations and the 12-lead electrocardiogram. The Seattle Angina Questionnaire (SAQ-7) shortened Rose Angina and EQ-5D-5L questionnaires will also be administered at baseline.

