### Long term follow-up assessments

All patients will be followed up until at least the required number of primary outcome events have accrued. This is expected to be a minimum of 24 months for each participant and a median of 36 months. Follow-up data will be collected remotely from medical records (and any future data linkage that may be necessary). Both the short version of the Seattle Angina Questionnaire (SAQ-7) and the European Quality of Life Five Dimension (EQ-5D-5L) questionnaire will be further administered at 3 months, 12 months and 24 months after randomisation. The SAQ-7 questionnaire has been validated in patients with coronary artery disease and shown to be sensitive to therapeutic interventions [23]. The EQ-5D-5L is a validated questionnaire measuring self-reported health status over time [24]. A lifestyle questionnaire recording body mass index, physical activity, smoking, diet, blood pressure, cholesterol and blood glucose will be administered together with the SAQ-7 and EQ-5D-5L questionnaires 24 months after randomisation (Table 2).

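### A normality rule, rather than a model named in advance, decides how SAQ-7 and EQ-5D-5L are analysed

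*Protocol article*

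**What the plan says.** The Statistical analysis section of the protocol article gives one generic rule for continuous secondary outcomes. The first branch is "linear regression for normally distributed continuous outcomes". The second is "Continuous outcomes that are not normally distributed will be analysed using appropriate nonparametric techniques". The section does not say how normality will be judged, or which nonparametric techniques are meant.

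Table 1 (Secondary endpoints) lists "Symptomatic status as assessed by the short form Seattle Angina Questionnaire (SAQ-7) up to 24 months of randomisation" and "Quality of life as assessed by the EQ-5D-5L up to 24 months of randomisation". Neither entry names an analysis time point or a summary measure.

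Both instruments are collected before follow-up starts ("EQ-5D-5L questionnaires will also be administered at baseline", in a sentence that also covers SAQ-7) and three times afterwards ("questionnaire will be further administered at 3 months, 12 months and 24 months after randomisation").

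Covariate adjustment is described only for the primary Cox model, "which will adjust for study site, age, sex and previous coronary artery disease". The section closes by deferring detail: "All statistical analyses will be pre-specified in a comprehensive statistical analysis plan". That plan is not at hand.

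**The concern.** Questionnaire scores with a fixed maximum rarely look normal, so the rule is likely to send SAQ-7 and EQ-5D-5L down the nonparametric branch. Two things are at stake.

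The first is the quantity being estimated. Regression gives a difference in mean score, in the units of the instrument. A rank comparison answers another question, roughly how often a participant in one arm scores higher than a participant in the other. Under the rule, the observed distribution chooses between them, which fits poorly with the promise to pre-specify all analyses.

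The second is precision. The trial already pays for a baseline score and three follow-up scores per participant. A regression or repeated-measures model can use all of them. A simple two-group rank test uses neither the baseline score nor the stratification factors.

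Whether CTCA improves symptoms or quality of life is a stated secondary objective, so the method for these two scores deserves a firm choice.

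**Working it through.** **Plan figure.** The article gives no standard deviation, target difference or power for SAQ-7 or EQ-5D-5L, so there is no figure on this point to reproduce. The group size used below comes from the Sample size calculation section. A two-sided comparison of 9% with 5.4% (a 40% relative reduction) at 90% power gives 1082 per arm, against 1081 stated.

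**Step 1: does non-normality matter at this size?** A simulation used 750 per arm, no treatment difference and 1000 runs for each of two assumed score shapes. In each run a Shapiro test was applied to the arm-centred values and a two-sample t-test compared the arms, both at 5%.

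| Assumed score | Normality rejected | t-test type I error |
|---|---|---|
| Normal, mean 80, SD 20, capped at 100 | 100% | 5.2% |
| Mildly skewed (gamma, shape 50) | 98.5% | 4.4% |

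The simulation error on a 5% rate is √(0.05 × 0.95 / 1000) = 0.7 percentage points, so both error rates agree with 5%. If normality is judged by a test, even mild skew would take a score out of regression, while the comparison of means remains valid.

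**Step 2: what is baseline adjustment worth?** Let r be the correlation between baseline and follow-up score. The documents do not give it, so 0.3 to 0.7 is assumed. Adjustment multiplies the variance of the treatment difference at one visit by 1 − r². The difference detectable with 90% power, in SD units, is (1.960 + 1.282) × √(2/n) × √(1 − r²). With n = 1081 and no adjustment this is 3.242 × 0.0430 = 0.139. The smaller group of 756 assumes a 70% questionnaire response (0.7 × 1081).

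| r | 1 − r² | Variance cut | Detectable, n = 1081 | Detectable, n = 756 |
|---|---|---|---|---|
| Unadjusted | 1.00 | – | 0.139 SD | 0.167 SD |
| 0.3 | 0.91 | 9% | 0.133 SD | 0.159 SD |
| 0.5 | 0.75 | 25% | 0.121 SD | 0.144 SD |
| 0.7 | 0.51 | 49% | 0.100 SD | 0.119 SD |

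**Step 3: what could the three visits add?** If every pair of occasions has the same correlation r, the baseline-adjusted average over the three follow-up visits has variance (1 + 2r)/3 − r², relative to one unadjusted visit. This is 0.44, 0.42 and 0.31 at r = 0.3, 0.5 and 0.7. An average over visits is a different summary from the difference at 24 months, so these figures show how much information is collected and are not the gain at any single visit.

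**The case against.** The strongest reply is that the article condenses a fuller plan. Two generic sentences cover every continuous secondary outcome, and covariates and visit structure are commonly left to the SAP. That stands for everything on which the article is silent. It does not dispose of the rule itself, which the article does state and which a SAP that follows it would inherit.

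Four stronger readings are tempting, and the documents do not support them.

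- A reader might infer that the baseline and repeated scores will be ignored. The article does not say so. Linear regression can include a baseline score, and nothing rules out a repeated-measures model.
- A reader might equate nonparametric techniques with unadjusted rank tests. No technique is named, and covariate-adjusted forms exist, such as rank analysis of covariance or bootstrap inference for an adjusted mean difference. Nor does the article say that normality will be decided by a significance test, or on raw scores rather than residuals.
- A reader might infer harm to the QALY estimate. The Cost-effectiveness analysis section derives QALYs separately, from the EQ-5D-5L measurements and survival times, under its own analysis plan.
- A reader might infer that participants without a 24-month score contribute nothing at 24 months, and that late recruits would be many of these. The article plans multiple imputation assuming data missing at random, which can draw on earlier visits. It also expects at least 24 months of follow-up for each participant. Any percentage put on this group would need accrual and closure assumptions that the documents do not give.

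It is also fair to say that chance baseline imbalance will be small with groups of this size. The argument for adjustment is therefore mainly one of precision.

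**Conclusion.** The point holds as a criticism of a stated rule. Making the method for SAQ-7 and EQ-5D-5L depend on normality is a weak choice. At this sample size it protects nothing that regression would not already protect, and it leaves the type of treatment effect open until the data are seen. The simulation supports this for two assumed score shapes and for normality judged by a test. With a looser judgement the routing is less certain, but the effect measure still depends on the data.

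The possible loss of precision is conditional. It arises only if the final analysis is in fact unadjusted, which the article does not say. In that case, baseline adjustment would cut the variance by 9% to 49% for correlations of 0.3 to 0.7, equivalent to 1/0.91 = 1.10 to 1/0.51 = 1.96 times as many participants. The loss from using a rank method in place of regression was not computed.

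The effect is confined to the precision and interpretation of secondary outcomes. No figure in the article is wrong on this point, and the primary result is unaffected.

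**What to change.** For SAQ-7 and EQ-5D-5L, replace the normality-dependent rule with one model named in advance:

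- a regression at each visit, or a repeated-measures model with treatment, visit and their interaction;
- adjustment for the baseline score and the stratification factors (age, sex, site and previous coronary artery disease);
- robust standard errors, so that skewness or a ceiling does not call for a change of method;
- the adjusted mean difference with its 95% confidence interval at 3, 12 and 24 months.

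Keep a rank-based analysis as sensitivity only. State how deaths are handled, because a standard mixed model treats scores after death as ordinary missing values. If the SAP already specifies such a model, confirm that it takes precedence over the generic sentence in the article.

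The change needs no new data or visits. It costs a few lines of SAP wording and slightly more analysis work.
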